## Abstract

Patients with severe mental disorders die on average 20 years prior to the general population. This mortality gap is mainly due to the higher prevalence of physical diseases and the adoption of unhealthy lifestyle behaviors.The LIFESTYLE trial aims to evaluate the efficacy of a new psychosocial group intervention (including psychoeducational, motivational, and problem-solving techniques) focused on healthy lifestyle behavior compared to a brief educational group intervention in a community sample of patients with severe mental disorders. The trial is a national-funded, multicentric, randomized controlled trial with blinded outcome assessments, which is carried out in six outpatient units of the Universities of Campania “Luigi Vanvitelli” in Naples, Bari, Genova, L'Aquila, Pisa, and Rome—Tor Vergata. All patients are assessed at the following time points: baseline (T0); 2 months post-randomization (T1); 4 months post-randomization (T2); 6 months post-randomization (T3); 12 months post-randomization (T4); and 24 months post-randomization (T5). T1 and T2 assessments include only anthropometric tests. The BMI, a reliable and feasible anthropometric parameter, has been selected as primary outcome. In particular, the mean value of BMI at 6 months from baseline (T3) will be evaluated through a Generalized Estimated Equation model. The work hypothesis is that the LIFESTYLE psychosocial group intervention will be more effective than the brief educational group intervention in reducing the BMI. We expect a mean difference between the two groups of at least one point (and standard deviation of two points) at BMI. Secondary outcomes are: the improvement in dietary patterns, in smoking habits, in sleeping habits, physical activity, personal and social functioning, severity of physical comorbidities, and adherence to medications. The expected sample size consists of 420 patients (70 patients for each of the six participating centers), and they are allocated with a 1:1 ratio randomization, stratified according to center, age, gender, and educational level. Heavy smoking, sedentary behavior, and unhealthy diet pattern are very frequent and are associated with a reduced life expectancy and higher levels of physical comorbidities in people with severe mental disorders. New interventions are needed and we hope that the LIFESTYLE protocol will help to fill this gap.

Trial registration number: 2015C7374S.

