## Anticipated results

### Primary outcome

BMI has been selected as primary outcome since it is a reliable and feasible anthropometric parameter, and it has already been considered in previous studies on lifestyle interventions (15, 16, 24). The primary outcome is the change of the BMI at 6 months post-randomization (T3). We expect a mean difference between the two groups of at least one point (and standard deviation of 2 points) at BMI. The work hypothesis is that the LIFESTYLE psychosocial group intervention will be more effective than the brief educational group intervention in reducing the BMI.

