### Secondary outcome

The secondary outcomes include an improvement in dietary patterns (i.e., a reduction in fat food and increase in consumption of fruits and vegetables), smoking habits (i.e., a reduction in the number of cigarettes smoked per day), sleeping habits (i.e., regular number of hours slept per night), physical activity (i.e., increasing in time spent walking per day), personal and social functioning (i.e., level of functioning and time dedicated to meeting friends), severity of physical comorbidities (i.e., reduction at the CIRS global score), and adherence to medications (i.e., reduction in changes in pharmacological doses and regimen).

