The implementation of a generalized estimated equation model (GEE). The GEE provides an estimation of the longitudinal impact of the interventions on primary and secondary outcomes, controlling for confounders, such as physical comorbidities, severity of psychiatric symptoms, level of social functioning, quality of life, self-esteem, recovery style, support from social network. A generalized estimating equation model will be employed using the following outcomes variables: the BMI, the severity index of the Cumulative Illness Rating Scale, the abdominal circumference: plasma levels of glucose, insulin, triglycerides, and cholesterol levels (total, LDL, and HDL); systolic and diastolic blood pressure, and cigarettes smoked per day.The development of a Structural Equation Model (SEM) in order to identify possible mediators and moderators of the efficacy of the interventions, controlling for several confounders such as age, gender, severity of symptoms, BMI, etc. In particular, the variable “duration of the intervention” will be tested as one of the most relevant mediator or moderator for the efficacy of the interventions.The implementation of multivariable logistic regression models, in order to identify predictors of positive response for changing unhealthy behaviors. In particular, as regards the primary outcome, this will be transformed in binary variable (yes vs. no) using the reduction of at least 1 point at the BMI as threshold. The impact of possible predictors (e.g., having an healthy diet; walking at least 30min per day; quitting smoking) as well as confounders (such as age, gender, level of education, diagnosis, duration of the illness, type of pharmacological treatment received) will be tested in a logistic regression model.A subgroups analysis, according to the different diagnostic groups, in order to identify different profiles of efficacy of the interventions. The hypothesis is that patients suffering from affective disorders (both major depression and bipolar disorders) will report a higher improvement in the reduction of BMI and in changing their unhealthy lifestyle behaviors compared to patients with schizophrenia.

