Non-adherence to medications is responsible for a variety of clinical and social problems, such as relapses, hospitalization, reduction in quality of life and in personal functioning [(77, 78)]; thus, improving medication compliance represents another important challenge addressed during the intervention. Since the LIFESTYLE intervention is patient-centered and motivational-led (78), it has been developed to fulfil the unmet needs of patients with severe mental illness, including the improvement of treatment adherence.

As regard our primary outcome measure, the BMI has been selected since it is a reliable and feasible anthropometric parameter to be analyzed. Of course, there are many factors which can have an impact on BMI changes, such as the pharmacological treatment (e.g., in the case of patients receive second generation antipsychotics) or other physical comorbidities (such as, endocrine diseases). We will be able to control for these possible confounders through multivariable statistical approach. Moreover, patients are required to identify a personal lifestyle goal to be achieved, and—by definition—such goal can be different for each participant, e.g., days spent in physical activities; drinking at least 2 l of water per day; reducing the number of cigarettes smoked per day; etc. and not easily measurable. In the experimental intervention, it has been included a brief session of moderate physical active at the end of each meeting, therefore we test the hypothesis that BMI can be reduced, even if the personal goal selected by the patient is related to smoking pattern or to other aspects of the lifestyle. As observed by Speyer et al. (22, 23), adopting an heterogeneous intervention, when every patient can choose the personal goal to be reached, can be the right choice for changing a complex phenomenon as lifestyle. The prevalence of unhealthy lifestyle behaviors is a transdiagnostic phenomenon and we decided not to tailor the intervention to a specific group of patients in order to involve the highest number of patients as possible. As recently pointed out (25) when the patient population is selected on the basis of the diagnoses, there are no data proving the higher efficacy of the lifestyle intervention.

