The trial has some limitations, which must be acknowledged. A first limitation is the selection bias of patients accepting to participate to the LIFESTYLE trial. In fact, it could be that only highly motivated patients accept to take part to the study and will continue to attend all scheduled sessions. Another possible limitation is the use of manuals for clinicians carrying out the intervention. While this methodological choice was made in order to increase external validity and reliability of the interventions, it may have limited the generalizability of the intervention to other patients. Moreover, the two interventions are different in terms of frequency of contact with the mental health professionals. This aspect will be considered as a potential confounder for the effectiveness of the intervention. Finally, another possible limitation of the study is the global duration of the intervention. In fact, Naslund et al. (80) recently highlighted that lifestyle interventions of ≥12-months duration appear to be more effective compared to those lasting ≤6-months. Moreover, other studies have found a modest or small effect for short-term interventions, suggesting that longer interventions should be studied. On the other hand, long approaches are associated with a higher drop-out rate of patients who may have difficulties in attending structured long-term approaches (81–84). Therefore, we will explore the efficacy and the effectiveness of a medium-term intervention with multiple follow-up assessments.

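### The GEE's listed confounders can be changed by the intervention and are not restricted to baseline values; contact frequency and on-study medication are also called confounders, and two listed covariates have no instrument

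*Protocol article*

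**What the plan says.** The primary outcome is defined in the Primary outcome section: "The primary outcome is the change of the BMI at 6 months post-randomization (T3"). The Abstract names the model: "the mean value of BMI at 6 months from baseline (T3) will be evaluated through a Generalized Estimated Equation model".

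The Data analysis section says that the GEE gives an "estimation of the longitudinal impact of the interventions on primary and secondary outcomes, controlling for confounders", and lists as examples "physical comorbidities, severity of psychiatric symptoms, level of social functioning, quality of life, self-esteem, recovery style, support from social network". It gives no measurement time for these covariates. Its only baseline reference to confounding variables is a check that the arms are homogeneous at T0.

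Several of these covariates are also outcomes. The Secondary outcome section lists "severity of physical comorbidities (i.e., reduction at the CIRS global score") and personal and social functioning. The Data analysis section names "the severity index of the Cumulative Illness Rating Scale" as an outcome of the same GEE. The Exploratory outcomes section lists BPRS symptom severity.

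Two further variables appear in the Discussion. After noting that the arms differ in how often patients meet professionals, it says: "This aspect will be considered as a potential confounder for the effectiveness of the intervention". After naming pharmacological treatment and physical comorbidity as influences on BMI, it says: "We will be able to control for these possible confounders through multivariable statistical approach". Neither statement says which model is meant.

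**The concern.** Randomisation already balances the arms in expectation, so the reason to adjust the efficacy comparison is precision, and baseline variables serve that purpose. A variable measured after randomisation can carry part of the treatment effect. Conditioning on it removes that part. It can also introduce bias if something unmeasured affects both that variable and BMI.

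The listed covariates are open to this problem. An intervention on diet, activity, adherence and daily rhythm may plausibly change comorbidity, functioning, symptoms and quality of life, and the trial itself counts some of these as outcomes. Contact frequency is a plainer case: it has no baseline value and is part of what distinguishes the arms. On-study medication is similar, because clinicians may adjust the regimen, adherence is a module of the experimental arm, and fewer regimen changes is how the adherence outcome is described.

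The stake is what the primary estimate means. The stated hypothesis is about the overall difference in BMI between the interventions. The text permits analyses that answer either that question or a narrower one, and does not fix the choice.

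**Working it through.** **1. Covariates against the rest of the article**

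| Covariate | Instrument (instrument lists, Table 3) | Times | Also an outcome? |
|---|---|---|---|
| Physical comorbidities | CIRS | T0, T3, T4, T5 | Secondary; GEE outcome |
| Psychiatric symptoms | BPRS | T0, T3, T4, T5 | Exploratory |
| Social functioning | Personal and Social Performance Scale | T0, T3, T4, T5 | Secondary |
| Quality of life | Manchester Short Assessment | T0, T3, T4, T5 | Not listed |
| Recovery style | RSQ | T0, T3, T4, T5 | Not listed |
| Self-esteem | None listed | – | Not listed |
| Social-network support | None listed | – | Not listed |

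Follow-up values of five covariates therefore exist and could enter a longitudinal model. The nearest items to the last two are the internalised stigma scale, the relationships area of the functioning scale, and number of family members. None is a stated measure of either construct.

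**2. The plan's own sample size**

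Inputs (Sample size and power calculation): difference 1, SD 2, two-sided alpha 0.05, power 90%, ICC 0.030, coefficient of variation of cluster size 0.400, 29 per arm per centre, six centres.

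- Independent patients: n per arm = 2 × [2 × (1.960 + 1.282) / 1]² = 84.06, so 85.
- Design effect = 1 + [(1 + 0.4²) × 29 − 1] × 0.03 = 1.979.
- 85 × 1.979 = 168.2 per arm, and 168.2 / 29 = 5.80, rounded up to 6 centres. This gives 174 per arm and 348 in total.
- Dropout: 29 / 0.85 = 34.1, so 35 per arm per centre and 420 in total.

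The 348 and 420 reproduce. Power at 174 per arm with this design effect is 0.912.

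**3. Baseline versus follow-up covariate**

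Let a be the effect of arm on the follow-up covariate and b the effect of that covariate on BMI. Total effect = direct effect + a × b. I fixed the total at −1 and a at 0.5, then set b = −0.5 (25% mediated) or b = −1 (50% mediated). I simulated 2,000 trials of 174 per arm with a linear model. The shares are assumptions, because the article gives none.

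| Assumed mediated share | Arm coefficient, T0 covariate | Arm coefficient, T3 covariate | Power with T3 covariate |
|---|---|---|---|
| 0% | −0.99 | −0.99 | 0.91 |
| 25% | −1.00 | −0.75 | 0.70 |
| 50% | −1.00 | −0.50 | 0.38 |

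The power column is a normal approximation with 174 / 1.979 = 87.9 effective patients per arm, SD held at 2, and an effect of 1 minus the share. For 25%: standard error = 2 × √(2 / 87.9) = 0.302; 0.75 / 0.302 − 1.96 = 0.53; power 0.70. Holding the SD at 2 ignores any precision gained from the covariate. The T3 coefficients simply return the assumed share. They show the mechanism and do not estimate bias in this trial.

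**4. Contact frequency, if it entered a model with arm**

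Arm I meets every 7–10 days for 5 months: 5 × 30.4 = 152 days, 152 / 10 = 15.2 and 152 / 7 = 21.7, so about 15–22 sessions. Arm II has 5. Scheduled contact is therefore nearly or wholly collinear with arm. For attended sessions I assumed 60–95% attendance and 15 or 21 sessions in Arm I, with and without extra variation between patients. The correlation with arm is then 0.73 to 0.995. The variance inflation factor 1 / (1 − r²) is about 2 to 95, and power for a 1-point difference is about 0.62 down to 0.05.

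**The case against.** The strongest reply is that the article never says follow-up values enter the GEE. Its only timing for confounding variables is baseline, and a condensed article may leave covariate timing to a fuller document. A scale can properly be a covariate at T0 and an outcome at T3. This stands, and it limits the point in several ways. A reader might infer any of the following, but the article does not support them:

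- **That the GEE cannot give the total effect.** With T0 values it does, as the working shows.
- **That the primary GEE contains contact frequency or medication.** Neither is in its list. The article names type of pharmacological treatment only for the logistic regression, and assigns intervention duration to the structural equation model as mediator or moderator.
- **That BMI at T1 and T2 would be lost because the questionnaires are not given then.** The plan carries the last observation forward, which read literally would fill those visits with T0 scores.
- **That self-esteem and network support were never collected, so the model cannot be fitted.** The article shows only that no instrument is listed. Its list is illustrative, so the model can be fitted without them.
- **That intention to treat is breached.** As used here, that principle concerns who is analysed and in which arm. Covariate choice changes what is estimated.

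The reply does not remove everything. The homogeneity check at T0 is not a rule for the model. A baseline reading cannot rescue contact frequency, which has no baseline value and is set by arm, so calling it a confounder is a conceptual error in the text as written. The promise to control for medication carries the same risk, because treatment may change during the study. Naming covariates without a listed source is also a defect of the text itself.

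**Conclusion.** The point holds in conditional form. The listed GEE covariates can respond to the intervention, five are re-measured at T3–T5, two are secondary outcomes, and nothing ties them to baseline. If T0 values enter, the arm coefficient estimates the total effect. If T3–T5 values enter, it becomes a partly direct effect: 0.75 or 0.50 of a 1-point difference under assumed mediated shares of 25% or 50%, with power of 0.70 or 0.38 instead of 0.91.

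Treating contact frequency or on-study medication as a confounder would, if carried into an efficacy model, remove part of the treatment effect. The article does not say that the primary model does this. The contact figures rest on assumed attendance and apply only if that step is taken. Self-esteem and social-network support lack a listed instrument.

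**What to change.** Amend the Data analysis section, and the two Discussion statements to match:

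- Limit covariates in the primary and secondary efficacy models to prespecified T0 values, with baseline BMI and the stratification factors (centre, age, gender, education).
- State that no post-randomisation variable (contact, attendance, medication change, T3–T5 scores) enters these models.
- Delete self-esteem and social-network support, or name the instrument and visits for each.
- Confine contact frequency and medication change to analyses labelled exploratory or mediation, and stop calling contact a confounder.
- Because Patients' recruitment has the randomisation code requested before the baseline assessment starts, confirm that T0 values are recorded blind to arm and before any session.

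The cost is wording. The five scales with a listed instrument, baseline BMI and the stratification factors are already available at baseline, and the sample size does not change. The wording should be settled before the outcome data are analysed.

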## Methods

### Design

The LIFESTYLE trial is a national-funded, multicentric, randomized controlled trial with blinded outcome assessments. The project has been funded by a grant of the Italian Ministry of Education, Universities and Research within the framework of the “Progetti di Rilevante Interesse Nazionale (PRIN) — year 2015”. It is a multicentric study involving the outpatient units of the University of Campania “Luigi Vanvitelli” in Naples, University of Bari, University of Genova, University of L'Aquila, University of Pisa, and University of Rome—Tor Vergata. The University of Campania “Luigi Vanvitelli” in Naples is the coordinating center, which has originally conceived the study's idea and design.

This is a randomized head-to-head comparison trial with two parallel arms for evaluating the efficacy and effectiveness of psychosocial group interventions in improving lifestyle behaviors in patients with severe mental disorders. The two interventions have been developed by the research staff and are both focused on the improvement of lifestyle behaviors.

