The intervention lasts 5 months and it is administered to groups of 5–10 patients every 7–10 days. The sessions cover the following topics: (1) healthy diet; (2) physical activity; (3) smoking habits; (4) medication adherence; (5) risky behaviors; (6) promotion of circadian rhythms. Each module includes the following components: (a) information on the risks of the specific unhealthy lifestyle and benefits in adopting healthy lifestyle; (b) teaching of practical strategies to change unhealthy behaviors; (c) identification of personal life goals for each participant, motivation to change, and problem-solving strategies. Sessions have been developed in order to stimulate discussion, work-groups and interaction among participants. At the end of each meeting, a 20-min session of moderate physical activity is scheduled (Table 1). The core feature of this intervention is the inclusion of the motivational component. During each session, group participants are supported by mental health professional in identifying a personal healthy lifestyle goal. After goal-definition, professionals help participant to define the motivations for lifestyle changing and teach problem-solving strategies for sustaining the behavioral change.

**Table 1 T1:** Programme of LIFESTYLE psychosocial group intervention.

Starting session: Introduction of the intervention, aims, purposes, presentation of participants, and definition of personal healthy lifestyle goals
Module 1: Diet, information on health food, principles, and benefits of healthy eating
Module 2: Physical activity, how to increase routine physical activity
Module 3: Smoking habits, information on the dangers of smoking, craving, difficulties for quitting smoking and consequences of long-term abuse of nicotine.
Module 4: Medication adherence, strategies for improving adherence, medical consequences of non-adherence
Module 5: Risky behaviors, sexually transmitted disorders, substance, and alcohol abuse
Module 6: Promotion of regular circadian rhythm, problems related to irregular daily activities
At the end of each meeting, a 20-min session of moderate physical activity (i.e., walking) is implemented with participants

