### Arm II: brief educational group intervention

The brief educational group intervention, which includes elements from the psychoeducational approach and from problem-solving techniques, consists of 5 weekly sessions and it is administered to groups of 5–10 patients. The following topics are covered: (1) healthy lifestyle; (2) early detection of clinical relapses; (3) effects of pharmacological treatment and management of side effects; (4) stress management techniques; (5) problem-solving techniques.

Manuals have been developed in order to ensure treatment fidelity among the different centers. Leaflets and other written materials are given to patients, whenever relevant. During the sessions, interaction among participants is supported using role-plays and work-groups (Table 2).

**Table 2 T2:** Programme of LIFESTYLE educational brief group intervention.

Starting session: Introduction of the intervention, aims, purposes, and presentation of participants
Module 1: Healthy lifestyle (e.g., healthy diet, physical activity, smoking habits, promotion of circadian rhythm)
Module 2: Early detection of psychiatric relapses
Module 3: Pharmacological treatment and management of side effects
Module 4: Stress management techniques
Module 5: Problem-solving techniques
Information and leaflets are provided to participants during each session. Positive changes are highlighted, potential strategies for change are discussed at each module. The main aim is to provide patients with the principles of healthy living (i.e., eating fruit and vegetable, drinking water, doing moderate physical activities, not abusing of alcohol, quit smoking, etc.)

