## Assessment time and instruments

Researchers participating to the study are blinded to patient allocation. All patients are assessed at the following time points: baseline (T0); 2 months post-randomization (T1); 4 months post-randomization (T2); 6 months post-randomization (T3); 12 months post-randomization (T4); and 24 months post-randomization (T5). T1 and T2 assessments include only anthropometric tests. All data will be collected through a paper and pencil interviewing and the expected time for filling in all assessment tools is about 60/90 min. During the completion of the assessment battery, whether patients feel distressed or exhausted, the assessment can be stopped and another appointment will be scheduled in the next 2/3 days with the researcher.

The following questionnaires and schedules will be used during the study (Table 3):

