In this study, we aim to evaluate the cost-effectiveness of the interventions, since only Verhaeghe et al. (79) found that the intervention is cost-effective only in men with a significant BMI reduction. For improving the dissemination of psychosocial interventions targeted on healthy lifestyle behaviors, it is necessary to prove that these interventions are cost-saving. In order to improve feasibility of the interventions in the clinical routine care, we decided not to include dieticians or physical trainers, since the involvement of health professionals different from psychiatrists or psychologists could hamper the dissemination of the interventions in the routine practice. Of course, this hypothesis should be further tested in multicentric studies involving different European countries, since it could be that workload and multidisciplinary staffs include different health professional according to the organization of the National health care. At least in Italy, the inclusion of specific health professionals such as dieticians and physical trainers is not the routine for the mental health care. A critical element in our research protocol is the attrition rate from the two intervention groups. As already pointed out in other studies on lifestyle psychosocial interventions, such as the CHANGE (22, 23) and CAPICOR (21) trials, the attrition rate ranges from 5 to 40% and we expect an attrition rate of at least 15%. Nevertheless, in order to guarantee attendance, patients will continue to be in contact with their referring clinicians during the provision of the intervention, and will receive phone or e-mail reminders for each session of the intervention. Moreover, the active involvement of patients as “experts” could further motivate them to attend the sessions during the intervention. This project represents the first multicentric randomized head-to-head comparison trial for evaluating the efficacy of psychosocial interventions targeting unhealthy lifestyle in people with severe mental disorders in Italy. In particular, we aim to test the efficacy of two different interventions targeting lifestyle behaviors. In particular, considering that one of the main critical issue is related to the optimal duration of the interventions, this aspect will be evaluated in our trial since we will test the impact of the “duration of the intervention”, as one of the possible mediator or moderator of the efficacy of the interventions.

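### Intervention duration is fixed by arm, so it cannot be tested as a mediator or moderator, and the trial cannot evaluate optimal duration

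*Protocol article*

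**What the plan says.** The Design section states: "This is a randomized head-to-head comparison trial with two parallel arms". No duration levels are randomised within an arm.

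For Arm I the article says: "The intervention lasts 5 months and it is administered to groups of 5–10 patients every 7–10 days". Arm II "consists of 5 weekly sessions and it is administered to groups of 5–10 patients".

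The Data analysis section lists a structural equation model for mediators and moderators, which is the second of the five secondary aims. It singles out intervention duration as a variable that "will be tested as one of the most relevant mediator or moderator for the efficacy of the interventions". The Discussion gives the reason: "one of the main critical issue is related to the optimal duration of the interventions, this aspect will be evaluated in our trial". It then repeats that duration will be tested as a possible mediator or moderator.

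The limitations paragraph acknowledges that contact frequency differs between the arms and says this will be considered a potential confounder.

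**The concern.** A moderator must vary among patients within an arm, so that the treatment effect can be compared across its levels. To separate a mediated from a direct effect, the mediator must vary among patients in the same arm. Planned duration does neither, because it is part of the definition of the arm.

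If the model is fitted as described, one of two things happens. With arm in the model, the duration parameters are not identified. With arm left out, the software returns an estimate that looks like a duration effect but is the overall arm contrast. A published statement on how long such programmes should last would then rest on a comparison that also reflects different content and a different number of contacts.

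**Working it through.** The article gives no figure to reproduce on this point. The question is whether the parameters can be estimated, and the design settles that.

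**Inputs**
- Two arms, 1:1 allocation, 420 patients (Design; Patients' recruitment; Sample size and power calculation).
- Arm I: 5 months, a session every 7–10 days.
- Arm II: 5 weekly sessions, so 5 × 7 / 30.44 = 1.15 months, taking 30.44 days per month.

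**Step 1: duration as a function of arm.** Let A = 1 for Arm I and 0 for Arm II, and let D be planned duration in months. Then D = 1.15 + (5 − 1.15)·A = 1.15 + 3.85·A. D is an exact linear function of A, so their correlation is 1.0.

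**Step 2: duration as mediator.** The path from D to BMI given arm needs the columns [1, A, D]. Because D is a linear combination of the other two, the rank is 2 where 3 is needed. The split into direct and indirect effects has no unique solution. A larger sample does not help, because the variance of D within arm is zero.

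**Step 3: duration as moderator.** The interaction needs [1, A, D, A·D]. Since D = 5 whenever A = 1, A·D = 5·A, another multiple of the arm column. The rank stays at 2 where 4 is needed.

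**Step 4: leaving arm out.** If BMI is regressed on D alone, the slope equals the arm difference divided by 3.85. With the planning difference of 1 BMI point, the model would report 1 / 3.85 = 0.26 points per month. The test statistic and p-value are those of the arm comparison, and no new information enters.

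**Step 5: can the arm contrast be read as duration?** The two intervention descriptions, side by side:

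| Feature | Arm I | Arm II |
|---|---|---|
| Length | 5 months | 5 weeks |
| Sessions | about 15 to 22 (152.2 days / 10 to / 7) | 5 |
| Motivational component | described as the core feature | not described |
| Exercise at each meeting | 20 minutes | not described |
| Modules on healthy living | all six address a lifestyle or health-behaviour topic | one of five is the healthy-lifestyle module |

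Several features change together with length, and two arms supply one contrast. That contrast cannot be divided among them.

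**The case against.** **Duration could mean exposure received.** Attendance varies between patients, and the 7–10 day spacing allows some variation in the number of sessions in Arm I. That would give within-arm variation and make some coefficient estimable. The article does not define the variable this way. The variation would also arise after randomisation and be non-randomised, and the limitations paragraph itself expects that highly motivated patients may be the ones who attend. Such an analysis can describe exposure but cannot show which duration is best. The article gives no attendance distribution, so no precision figure can be put on it.

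**Contact frequency is already acknowledged.** This is true, but calling it a confounder does not separate it from arm, and the content differences remain.

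**The claim is modest.** The Discussion says that duration will be evaluated, not that an optimum will be established, and calls it a possible mediator or moderator. This stands as a limit on seriousness. It does not make the model estimable.

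**Detail belongs in the full plan.** Model specification does. The aliasing does not, because it follows from the two arm definitions and no further specification of planned duration can remove it.

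**A reader might also infer a time-order fault.** The reasoning would be that "T1 and T2 assessments include only anthropometric tests", so behavioural mediators are first repeated at 6 months, together with the primary BMI measurement. The document does not support calling this an error. The Data analysis section names no visit for the structural equation model, and BMI is also measured at 12 and 24 months.

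**Conclusion.** The point holds for planned duration, which is the plain reading of the text. The correlation with arm is exactly 1, and neither the mediator nor the moderator parameter can be estimated. This rests only on the two stated arm lengths and the absence of randomised duration levels, with no numerical assumption beyond converting weeks to months. Because content and contact frequency also differ by arm, the statement that optimal duration will be evaluated is not supported by the design.

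A reader might infer that the trial's main conclusion is at risk. It is not. The primary outcome is BMI at 6 months, compared between arms as randomised, and duration plays no part in that comparison. What is affected is part of one secondary aim and a claim in the Discussion. The analysis should be changed, but the trial's main inference does not depend on it.

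**What to change.** - Remove intervention duration from the structural equation model, both as mediator and as moderator.
- Restrict moderators to baseline variables, each tested as an arm-by-covariate term.
- Withdraw the Discussion statement that optimal duration will be evaluated. State instead that the trial compares two programmes differing in length, content and contact.
- If exposure is of interest and attendance was recorded, analyse sessions attended within each arm, labelled exploratory and non-randomised.
- Do not use randomisation as an instrument for sessions attended. That would require arm to affect BMI only through the number of sessions, and the motivational and exercise components contradict this. The result would again be the arm effect divided by a difference in dose.

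The cost is a change of wording and one secondary claim given up. The primary analysis and the visit schedule stay as they are. The optional exposure analysis depends on records that the article does not mention. Interventions were already being delivered when it was written, so attendance at past sessions may not be recoverable if it was not recorded.
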